**Fig. 2 Fig2:**
[figure not shown]
Process improvement

Multiple patients, primary care providers, and staff engaged with the SAC through development of this virtual SDM intervention, a previous pilot study, and planning for this current implementation study in primary care are involved in process improvement. We plan to use an iterative quality improvement method, where the implementation will be adjusted at each practice based on feedback from the SAC after advisory members are updated with ongoing outcomes and survey results.

Domains from the CFIR [90–94], such as inner setting (structural characteristics, culture, networks and communications, and tension for change) and outer setting (patient needs and resources, external policies, and incentives), will be incorporated into the implementation evaluation surveys (see Additional files 1, 3–5) [95–97]. The RE-AIM framework represents a flexible, comprehensive model according to which we will execute and evaluate the SDM implementation (Fig. 3). Adapting RE-AIM elements allows for full evaluation of the intervention at different time points during the study [98, 99].

**Fig. 3 Fig3:**
[figure not shown]
Conceptual model

Results from the RE-AIM-guided evaluation at baseline, during, and after the intervention will use outcomes data and participant input to inform implementation reach and assess barriers and facilitators, allowing for process adjustments (Table 3). CFIR survey measures and the Organizational Readiness for Implementing Change (ORIC) measure [95, 96, 100] will be used to assess collective perceptions about factors expected to affect implementation of Coach McLungs^SM^ (see Additional files 1–5).

**Table 3 Tab3:** RE-AIM evaluation tools and measures by specific aim

Specific Aim 1: Primary care implementation and evaluation of *Coach McLungs*^*SM*^
Sub Aim 1.2 Implement the *Coach McLungs*^*SM*^ SDM intervention into 21 primary care practices
Sub Aim 1.3 Evaluate barriers and facilitators to implementation at practice and system level

Sub Aim	RE-AIM	Measures	Evaluation tools	# of months per practice			
				0	6	12	18
1.2	Reach and Implementation	Providers and Administration	CFIR / ORIC Survey (Pre-Implementation) 21 Practices	×			
1.3	Adoption and Implementation	Providers, Staff, Patients	Key Informant Interview 3 Practices		×		
		Providers	SDM-Q-Doc Survey 3 Practices			×	
		Providers	CFIR Survey (Post-Implementation) 3 Practices		×	×	×

Specific Aim 2: Conduct on-going evaluation of patient-centered outcomes						
RE-AIM	Measures	Evaluation tools	# of months per practice			
			0	6	12	18
Reach and Maintenance	Patients	*Coach McLungs*^*SM*^ use compared to the total # of eligible patients		×	×	×
Adoption	Patients	*Coach McLungs*^*SM*^ Completion %		×	×	×
Effectiveness	Health Utilization Outcomes	ED Visits, Hospitalizations, Oral Steroids, Exacerbations, and PCP Utilization	×	×	×	×
Adoption (Built-in Surveys)	Knowledge, Satisfaction, and Self-Efficacy	Patient Surveys		×	×	×
Reach and Maintenance	Providers	# of Providers using *Coach McLungs*^*SM*^		×	×	×

Reach will be considered the recruitment and retention of practices and providers in the study and the number of patients using Coach McLungs^SM^. Reach will also be the number of practices receiving the training for Coach McLungs^SM^ at kick-off, and the number and proportion of patient and providers at each practice receiving the intervention. Effectiveness will be based on health utilization outcomes. Patient utilization data of acute care visits for asthma exacerbations will be analyzed. Adoption will be based on the acceptability, barriers and facilitators to successful adoption of the intervention among participants. For patients’ adoption will be considered the number of patients who complete use of Coach McLungs^SM^ and the number of optional shared decision making knowledge, attitude, and self-efficacy asthma surveys built-in to Coach McLungs^SM^ [101]. The patient/caregiver user is prompted to complete the asthma surveys immediately after each initial coaching visit (see Additional file 8). For providers, we will use the validated 9-item questionnaire (SDM-Q-DOC) (see Additional file 9), and CFIR implementation evaluation surveys (see Additional file 1, 3–5), and key informant interviews (see Additional file 7), to determine the acceptability, barriers and facilitators to successful adoption from physicians’ perspectives [102, 103]. Implementation will be evaluated using ORIC surveys to assess practice readiness to implement change (see Additional file 2). Provider CFIR surveys will take place pre-implementation and post-implementation (see Additional files 1, 3–5). Maintenance number of recorded uses of Coach McLungs^SM^ will evaluate sustainability.

Anticipated barriers to Reach are based on our prior implementation knowledge of the need for practices to have flexibility in their approach to implementation. By using a tailored approach [99], we anticipate to fully and effectively implement Coach McLungs^SM^ at all 21 practices. We will (1) use a flexible approach with practices that includes a 6-month step time window in order to mitigate circumstantial barriers such as practice availability for kick-off; (2) address staff and provider preferences for each practice, such as who is needed at meetings, does the practice want a staggered or practice-wide approach to implementation; (3) the practice may request extra support for items such as extra training for communication skills (usually motivational interviewing or shared decision making), use of asthma guidelines, asthma medication management education; (4) practices may request support in considering how to adapt flow and timing of patient visits in order to maximize use of Coach McLungs^SM^. The implementation training will be adapted from the ERIC (Table 4).

**Table 4 Tab4:** Implementation plan based on expert recommendations for implementing change (ERIC)

ERIC element	Element description for *Coach McLungs*^*SM*^ implementation
Use data experts	Director of data analytics will lead team to acquire, manage, and report data generated by implementation effort
Provide local technical assistance	Practice rollouts will be conducted by the lead research team with the implementation team providing technical assistance
Audit and provide feedback	Develop individual primary care practice feedback summaries including CFIR results and combined performance at other implementation and control sites and report out to practices at 6- 12- and 18- months post-implementation based on their preferences which include but no limited to: email, webinars, lunch-and-learn meetings and Skype conference calls
Use an implementation advisor	An implementation team will advise on the use of implementation frameworks and evaluation plan
Implementation facilitation	The lead reach team are both experienced practice facilitators with both *Coach McLungs*^*SM*^ and the previous paper-based asthma SDM toolkit
Assess for readiness and identify barriers and facilitators	Organization readiness assessment will take place at the system and practice level using the ORIC tool and elements from CFIR. Practice leadership, providers and patients will be surveyed and/or interviewed to evaluate barriers and facilitators
Develop an implementation blueprint	Manual of operation procedures will be developed to guide implementation strategies and goals
Organize implementation teams	The lead reach team will organize the implementation teams
Conduct educational outreach and ongoing training	Rollouts include kick-off lunch-and-learns consisting of 45-min training in patient/provider SDM communication, asthma guidelines and inhaler use refresher, and the use of *Coach McLungs*^*SM*^. Additional education training is based on practice needs and interest
Conduct educational meetings	The SAC will meet regularly, and other educational sessions will be targeted towards multiple stakeholders e.g. providers, practices adopting *Coach McLungs*^*SM*^, administration, community members, patients/caregivers
Engage community resources	Connect practices and patients to community resources with community partners

### Consent process

Since participant interviews are voluntary and will be anonymous, a waiver of documentation will be submitted to the IRB requesting that documentation of consent/assent will not be required. All staff involved in recruitment and retention will be required to successfully complete Human Subjects training and Health Insurance Portability and Accountability Act (HIPAA) training prior to working on this project.

Consent/assent forms describing in detail the study intervention, study procedures, and risks will be given to the participant. The following consent/assent materials are submitted with this protocol:Patient Informational Leaflet for Key Informant Interview.Provider Informational Leaflet for Key Informant Interview.

A verbal explanation will be provided in terms suited to the participant’s comprehension of the purposes, procedures, and potential risks of the study and of their rights as research participants. Participants will have the opportunity to carefully review the consent/assent form and ask questions prior to providing consent/assent for the study. Participants must be informed that participation is voluntary and that they may withdraw from the study at any time, without prejudice. A copy of the consent/assent document will be given to the participants for their records. The consent/assent process will be conducted and documented in the source document (including the date) before the participant undergoes any study-specific procedures. The rights and welfare of the participants will be protected by emphasizing the quality of their medical care will not be adversely affected if they decline to participate in this study.

### Study design

The stepped-wedge design is useful for the evaluation of complex healthcare interventions [89], particularly when the intervention is believed to be beneficial with minimal risk [104]. This design is increasingly being used to evaluate interventions involving healthcare delivery due to: (1) allowing the research team and clinical teams to rollout the intervention in small number of facilities in a timely, systematic manner [105]; (2) increasing participation and buy-in since all facilities will eventually get to implement the intervention during the study [89, 106, 107]; and (3) increase in statistical power compared to a cluster randomized trial due to increase in data collection and within cluster comparisons [89]. Our intervention is applied at the practice (cluster) level but the exacerbation rates are obtained on patients. In this cross-sectional cohort design, we will include both patients who are present at baseline and new patients coming into the practice throughout the study period. All patients in a practice would be eligible but providers may decide that some patients do not need to utilize Coach McLungs^SM^ [108].

### Sample size justification

We used a method to estimate sample size that takes into account the cluster randomization and the stepped-wedge design [88]. Our study design includes 21 clusters (facilities) with 6 time periods (including the baseline), 5 steps, 4 facilities switching from control to intervention at each step (except the third step will have 5), and an average of 30 patients per practice being continuously followed. Thirty patients is conservative as the typical number in a 6-month period is approximately 100. We conducted sample size analyses accounting for intracluster correlation (ρ = 0.20), individual autocorrelation (τ = 0.5), and cluster autocorrelation (π = 0.9) [88]. This design achieves 84% power to detect the hypothesized effect size difference of 10% in overall exacerbation between control (40%) and intervention (30%) periods (two-sided, α = 0.05). An effect size of 0.1 translates to a difference between groups of 10% absolute difference between intervention and control overall exacerbation rates.

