## Methods

We propose cross-sectional stepped-wedge cluster randomized design with a phased, randomized rollout. Twenty-one practices will be assigned the intervention randomly over the course of 30 months with the first 6 months used as a baseline period (total rollout time period 36 months) [88]. The research team will be blinded to practices that will receive the intervention until 3 months prior to implementation. Randomization is generated by the study statistician using SAS version 9.4, stratified by practice size (Table 1). Once the intervention has been rolled out at the practice, patients will be exposed to Coach McLungs^SM^ as they are seen by providers for their asthma. This implies that crossover to the intervention is not only at the practice level but also potentially the patient level [89]. The patient level exacerbation rates will be measured at 6-, 12-, and 18-month intervals pre- and post- the interaction with Coach McLungs^SM^.

**Table 1 Tab1:** Stepped-Wedge Design for *Coach McLungs*^*SM*^ Implementation with 6-month time intervals for each

	**Baseline (6 mos)**	*Time 1 (6 mos)*	*Time 2 (6 mos)*	*Time 3 (6 mos)*	*Time 4 (6 mos)*	*Time 5 (6 mos)*
Practices 1–4	**120**	*120*	*120*	*120*	*120*	*120*
Practices 5–8	**120**	**120**	*120*	*120*	*120*	*120*
Practices 9–13	**150**	**150**	**150**	*150*	*150*	*150*
Practices 14–17	**120**	**120**	**120**	**120**	*120*	*120*
Practices 18–21	**120**	**120**	**120**	**120**	**120**	*120*

Bold: control period, Italics: intervention period

The aim of implementation is to disseminate Coach McLungs^SM^ to patients most at need in the primary care setting. Often these patients have problems with managing asthma as a chronic disease and adhering to treatment plans. Primary care providers and staff are aware of the need to better prepare patients for chronic asthma management and fully support the Coach McLungs^SM^ SDM intervention.

Inclusion Criteria for this study are: (1) having attained the age of at least 5 years but less than 18 years at enrollment; (2) having established mild, moderate, or severe persistent asthma with a diagnosis verified by practice providers; (3) English or Spanish speaking. 4,981 patients in 21 practices aged 5–17 were seen in primary care for asthma in last 18 months (Table 2).

**Table 2 Tab2:** Number of Primary Care Patients Age 5–17 Diagnosed with Asthma October 2017 to March 2019

	# Eligible patients at proposed 21 practices	# Patients in healthcare system

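### The stated 84% power does not follow from its stated inputs under the planned model, which gives about 93–95%; the source of the 84% cannot be identified, and the sampling labels need reconciling

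*Protocol article*

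**What the plan says.** The inputs stand in the Sample size justification section of the protocol article:

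- Layout: "Our study design includes 21 clusters (facilities) with 6 time periods (including the baseline), 5 steps", with "4 facilities switching from control to intervention at each step (except the third step will have 5").
- Patients: "an average of 30 patients per practice being continuously followed". Table 1 agrees: 120 per group of four practices and 150 for the group of five, in every period.
- Correlations: "intracluster correlation (ρ = 0.20"), "individual autocorrelation (τ = 0.5), and cluster autocorrelation (π = 0.9").
- Effect: "effect size difference of 10% in overall exacerbation between control (40%) and intervention (30%) periods", tested two-sided at 0.05.

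The result is 84% power, repeated in the Abstract. The Analysis of outcomes section specifies a mixed model with fixed effects for intervention and time, random effects for practice and practice-by-time, and a further random effect for each patient to handle repeated measures.

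The sampling scheme is described in three ways. Methods: "We propose cross-sectional stepped-wedge cluster randomized design with a phased, randomized rollout". Study design: "In this cross-sectional cohort design, we will include both patients who are present at baseline and new patients". Sample size justification: patients under continuous follow-up, with a non-zero individual autocorrelation.

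**The concern.** This is the article's only quantitative justification of the trial's size. Every input is printed except the outcome variance, the reference distribution and how the correlations behave over time, so a reader should be able to get close to 84%. Under the model that the article itself names, that is not possible.

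The inputs also sit awkwardly with the labels. An individual autocorrelation has meaning only if the same children are measured in more than one period, and a purely cross-sectional design has none. How far patients overlap changes the standard error materially. It also decides what the figure of 30 stands for and how much the patient random effect has to do.

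**Working it through.** **Inputs from the article.** 21 practices allocated 4/4/5/4/4 to five steps; 6 periods; n = 30 per practice-period; ρ = 0.20; π = 0.9; τ = 0.5; difference 0.10; two-sided 0.05.

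**Assumptions, because the article does not give them.** The outcome variance s² runs from 0.225 (the mean of 0.4×0.6 = 0.24 and 0.3×0.7 = 0.21) through 0.24 (control rate) to 0.25 (the maximum for a proportion). The reference is normal, or t on 21 − 2 = 19 df. The calculation is on the risk-difference scale.

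**Model.** Random practice, practice-by-time and patient effects imply a correlation between periods that does not depend on the time lag. For cluster-period means:

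- variance = s²[ρ + (1 − ρ)/n]
- covariance between any two periods = s²[ρπ + (1 − ρ)τ/n]

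The variance of the intervention effect comes from generalised least squares with fixed period effects. Power = Φ(0.10/SE − 1.96), or the t equivalent with 2.093.

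**Attempt to reproduce 84% from the stated inputs.** At s² = 0.225, SE = 0.0275 and 0.10/SE = 3.63, so power is Φ(1.67) = 95.3%.

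**Closed-form check (equal steps).**

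- Design effect for clustering: 1 + 29×0.20 = 6.8.
- Correlation of cluster means between periods: r = (30×0.20×0.9 + 0.80×0.5)/6.8 = 5.8/6.8 = 0.853.
- Design effect for repeated assessment, L = 5: 3L(1 − r)(1 + Lr)/[(L² − 1)(2 + Lr)] = 15×0.147×5.265/(24×6.265) = 0.0772.
- SE = √[4×0.225/(21×30) × 6.8 × 0.0772] = 0.0274; power 95.5%.

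The two methods agree. Generalised least squares over the assumed range gives:

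| Reading | s² = 0.225 | 0.24 | 0.25 |
|---|---|---|---|
| Stated inputs, planned model, normal | 95.3% | 94.0% | 93.1% |
| Stated inputs, planned model, t 19 df | 93.0% | 91.5% | 90.4% |
| τ = 0, constant correlation, normal | 87.0% | 84.8% | 83.3% |
| τ = 0, constant correlation, t 19 df | 83.3% | 80.9% | 79.2% |
| Stated τ and π, both decaying with lag, t 19 df | 86.3% | 84.1% | 82.6% |

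In the last row the covariance at lag k is s²[ρπᵏ + (1 − ρ)τᵏ/n].

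**Other routes close to 84%.** Partial overlap (τ = 0.25, constant correlation, s² = 0.25, t on 19 df) gives 84.9%. A constant π of about 0.81–0.84 with τ = 0.5 and a normal reference gives 84%.

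**Size of the overlap effect.** At s² = 0.225, SE is 0.0275 with full overlap (τ = 0.5) and 0.0324 with none (τ = 0).

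**The case against.** The calculation is attributed to a cited method that is not shown, and an article condenses such detail. A decaying correlation structure or a small-sample correction may have been used, and together they can give about 84% from the printed τ and π. That stands as a reason not to diagnose the cause. It does not rescue the figure, because decay is not the structure that the Analysis of outcomes section implies and the article names no such choice.

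A reader might infer that 84% can arise only if patients are not repeated, so that it must belong to a purely cross-sectional calculation. The documents do not support this. With τ = 0, power runs from 79% to 87% depending on variance and reference distribution, neither of which is fixed, and several readings with repeated patients come as close.

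A reader might also take the continuous follow-up wording to mean a closed cohort. An average number under follow-up is compatible with turnover. Read with the inclusion of new patients and the patient random effect, the text points to an open cohort with a loose cross-sectional label.

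Finally, the error is conservative, and the article calls 30 patients conservative against a typical 100 or so per 6 months. Both points stand and limit the urgency.

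**Conclusion.** The point holds as a reporting error. Under the planned model the printed inputs give about 93–95% power (normal reference, variance 0.225–0.25) or 90–93% (t on 19 df), not 84%. No variance or reference distribution in that range brings the planned model down to 84%. The conclusion rests on constant between-period correlation, as the stated random effects imply, and on a linear approximation for a binary outcome.

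The trial is not shown to be underpowered for 40% versus 30%; on this account the stated figure understates the power. That reassurance depends on the same model: decaying correlations would lower the power, to 89.6% with the stated τ and π at variance 0.225, and to 75–80% with no patient overlap (normal reference in both cases). The origin of the 84% remains unknown. The three descriptions of the sampling scheme are inconsistent as worded, although together they are best read as an open cohort.

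**What to change.** - Rerun the power calculation for the model in Analysis of outcomes. Restate the result in Sample size justification and in the Abstract, naming the correlation structure, outcome variance and reference distribution used.
- Describe the design as an open cohort in Methods, Study design and Sample size justification, and say what the average of 30 counts.
- Because overlap in an open cohort is not known in advance, report power for 40% versus 30% as a range: about 83–87% with no overlap to about 93–95% with full overlap (constant correlation, normal reference). Add that correlations decaying over time would lower both ends.
- Do not set τ = 0 merely to keep 84%. That would fit an input to a result and contradict the patient random effect.

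The cost is one rerun calculation and a few edited sentences. The number of practices and the analysis model stay as they are.

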## Discussion

### Anticipated outcomes

All practices (100%) will receive a lunch-and-learn training on SDM communication and implementation of Coach McLungs^SM^. We assume 70% of patients and providers will begin adopting the intervention Coach McLungs^SM^. We expect that 50% of patients and providers patients will still be using Coach McLungs^SM^ by the end of the study.

Exacerbation outcomes will be measured over 18 months consisting of: ED visits, hospitalizations, and oral steroid prescriptions. We anticipate reductions in the proportion of intervention asthma patients with ED visits from 10 to 8%, patients with hospitalizations from 1.1% to 1.0%, with oral steroid prescriptions from 35 to 30%, and patients with a composite exacerbation outcome defined as having one or more of ED visits, hospitalizations, and patients with oral steroid prescriptions will decrease from 40 to 35%. Results of asthma outcomes for each practice will be presented to the practice at the 12-month post kick-off visit along with comparison aggregate data from the other implementation and control sites.

Safety oversight will be under the direction of a Data and Safety Monitoring Board. The DSMB will provide its input to National Institutes of Health staff.

Stakeholder engagement will prove valuable for identifying and addressing barriers to implementation, dissemination, and incorporation of results into practice. Ineffective communication [110, 111], low cultural competence [112], and lack of humility [113] are key barriers when working with vulnerable patients with low income, children, and minority groups [114–117].

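### The 84% power is for a fall from 40% to 30%, but the article forecasts 40% to 35% for what appears to be the same composite; power for that fall is about 43% on the stated inputs

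*Protocol article*

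**What the plan says.** The Sample size justification states: "This design achieves 84% power to detect the hypothesized effect size difference of 10% in overall exacerbation between control (40%) and intervention (30%) periods". The abstract repeats this claim. The significance level for the calculation is given as "two-sided, α = 0.05". The section makes clear that the effect is on the absolute scale: "An effect size of 0.1 translates to a difference between groups of 10% absolute difference between intervention and control overall exacerbation rates". Its inputs are 21 practices, 6 periods including baseline, 5 steps (4 practices each, 5 at the third), 30 patients per practice, intracluster correlation 0.20, individual autocorrelation 0.5 and cluster autocorrelation 0.9. It calls 30 patients conservative and about 100 per 6-month period typical.

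The Discussion, under Anticipated outcomes, gives a different figure. Its composite counts any patient with at least one of the three events, and the forecast is that "patients with oral steroid prescriptions will decrease from 40 to 35" percent. The window is also given there: "Exacerbation outcomes will be measured over 18 months consisting of: ED visits, hospitalizations, and oral steroid prescriptions". The component forecasts are ED visits 10% to 8%, hospitalizations 1.1% to 1.0% and oral steroids 35% to 30%. On uptake the same section says: "We assume 70% of patients and providers will begin adopting the intervention". It expects 50% still to be using the tool at the end of the study.

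**The concern.** One article gives two intervention-period rates, 30% and 35%, against the same 40% control rate. The sample size rests on the larger effect, which is twice the forecast one. If the forecast is what the investigators expect, the headline power does not describe the trial's chance of detecting it. A reader who relied on 84% could then give a non-significant result more weight against a benefit than it deserves.

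**Working it through.** **Inputs.** From the Sample size justification: steps of 4, 4, 5, 4, 4 practices; 6 periods; m = 30 (or 100) patients per practice-period; ρ = 0.20; π = 0.9 (cluster autocorrelation); τ = 0.5 (individual autocorrelation); two-sided α = 0.05. As a sensitivity, τ = 0, because the Methods section calls the design cross-sectional. τ = 0 is not a stated input.

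**Model.** Generalized least squares on practice-period means with fixed period effects. The covariance of one practice's six means is

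σ² × [ρπ·J + ρ(1−π)·I + ((1−ρ)/m)·(τ·J + (1−τ)·I)],

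where J is the all-ones matrix and I the identity. At m = 30 the design effect for clustering is 1 + 29 × 0.20 = 6.8. The correlation between two period means of one practice is (30 × 0.20 × 0.9 + 0.8τ)/6.8, which is 0.853 for τ = 0.5 and 0.794 for τ = 0. The variance of the intervention effect is v × σ², with:

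| | τ = 0.5 | τ = 0 |
|---|---|---|
| v, m = 30 | 0.003367 | 0.004671 |
| v, m = 100 | 0.002435 | 0.002833 |

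Power = Φ(d/SE − 1.96), with SE = √(v·σ²).

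**The article's own figure (40% v 30%, m = 30).** Pooled variance: σ² = 0.35 × 0.65 = 0.2275.
- τ = 0.5: SE = 0.0277; 0.10/0.0277 = 3.61; power 95% (93–95% over pooled, control-rate and maximum binary variance).
- τ = 0: SE = 0.0326; 0.10/0.0326 = 3.07; power 87% (85% with control variance 0.24, 83% with maximum variance 0.25).

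The stated inputs therefore do not return 84% under this model. A figure near 84% appears only with τ = 0.

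**The forecast effect (40% v 35%).** σ² = 0.375 × 0.625 = 0.2344.

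| | τ = 0.5 (stated) | τ = 0 (sensitivity) |
|---|---|---|
| m = 30: SE | 0.0281 | 0.0331 |
| m = 30: power | 43% | 33% |
| m = 100: SE | 0.0239 | 0.0258 |
| m = 100: power | 55% | 49% |

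With unlimited patients per practice, power levels off at about 63% under the stated ρ and π.

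**Check that does not use the model.** An 84% power for 0.10 implies SE = 0.10/(1.960 + 0.994) = 0.0338. For 0.05 that gives Φ(0.05/0.0338 − 1.96) = 31%. The SE is held fixed here.

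**Difference detectable with 80% power**, with the variance evaluated at that difference:

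| | τ = 0.5 | τ = 0 |
|---|---|---|
| m = 30 | 7.8 points | 9.2 points |
| m = 100 | 6.7 points | 7.2 points |

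The forecast 5 points lies below all four.

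**Is 35% a slip?** In the control forecast, 40% − 35% = 5% of patients enter the composite without a steroid prescription. In the intervention forecast, 35% − 30% = 5% again. A composite of 30% would leave 30% − 30% = 0% in that group, although ED visits are forecast to fall only from 10% to 8%. The section's forecasts are therefore coherent with 35%. This shows internal consistency only; it is not independent evidence against 30%.

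**The case against.** - **The 10 points could be a target difference rather than a forecast.** The article itself calls it hypothesized and gives no rationale based on a smallest important difference, so this does not reconcile the figures.
- **The outcomes may differ.** The sample size section speaks of overall exacerbation and the design has 6-month periods, whereas the forecast is over 18 months. This stands as a caveat: sameness is inferred from the 40% control rate and the three components, which the abstract also names. If the windows do differ, the 6-month planning rate of 40% needs its own explanation.
- **The low end of the power range is not on the stated inputs.** Correct: 33% needs τ = 0, whereas the article states 0.5 and adds a patient random effect to its model. The stated inputs give 43%.
- **A reader might infer that the trial will more likely than not end non-significant.** The documents do not support that generally. At the typical 100 patients with τ = 0.5, power is 55%.
- **A reader might infer further dilution**, because uptake is assumed to go from 70% to 50% and outcomes are analysed in all asthma patients whether or not they used the tool. The article does not say whether the 5 points apply to users or to everyone in the intervention period; the forecast may already reflect uptake.
- **Misreading of a null result is softened**, since the analysis section promises a mean difference with a 95% confidence interval. That is fair; the interval would show whether 5 points is excluded.

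**Conclusion.** The contradiction is explicit: the same 40% control rate is paired with 30% in the abstract and sample size section and with 35% in the Discussion. The 84% does not apply to the forecast 5-point fall. Power for that fall is about 43% at 30 patients per practice-period and about 55% at 100 on the stated correlations, about 33% and 49% with τ = 0, and about 31% if the SE is taken from the stated 84%. These figures rest on a normal-approximation model for a risk difference, on the two passages describing the same outcome, and on the 18-month forecast being carried into a 6-month-period design. The 84% is itself unexplained, because the stated inputs give about 95%. The point goes no further: it does not establish that the trial will probably fail, or that the effect will be smaller than 5 points.

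**What to change.** Use one planning effect and one outcome window in the abstract, the Sample size justification and Anticipated outcomes. Either restate power for 40% v 35%, or correct the forecast and justify 30%. With that change:

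1. State how the 84% was obtained, and in particular whether the individual autocorrelation of 0.5 was used, before printing a replacement figure.
2. Give the difference detectable with 80% power: about 7.8 points (τ = 0.5) and 9.2 (τ = 0, labelled as a sensitivity) at 30 patients; about 6.7 and 7.2 at 100.
3. Say whether the planning effect is practice-wide, after the assumed 70% and 50% uptake, or applies to users only.
4. State that a non-significant result would not by itself exclude a 5-point benefit.

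The cost is text only, with no change to practices or patients. If 35% is kept, the downside is a less favourable stated power.
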